*C unshiu* peel and *C pinnatifida* fruit have been widely used for hundreds of years in traditional Chinese and Korean medicine, and have attracted increasing attention as promising agents for the treatment and prevention of obesity and metabolic diseases.^[5,6]^ The antiobesity and lipid-lowering effects of the 2 herbs have been well documented in experimental studies.^[6–8]^ Furthermore, *C unshiu* lowered BMI and improved lipid profiles in overweight and obese subjects,^[9]^ and a *C pinnatifida*-based herbal formula reduced plasma low-density lipoprotein cholesterol levels in dyslipidemic patients.^[10]^ Our previous animal studies showed more effective reduction in high-fat diet-induced body weight gain when *C unshiu* and *C pinnatifida* were combined compared to the individual herb.^[11]^ Their combination, HT048, reduced body weight, and adiposity to levels comparable to those in the orlistat, an antiobesity drug, -treated group and improved dyslipidemia in obese rats.^[11]^

*N nucifera* leaf has been traditionally used as folk medicine for the treatment of obesity, hyperlipidemia, and hyperglycemia in China,^[12,13]^ and *P persica* flower has been consumed as a tea for weight reduction in China and Korea.^[14]^ In preclinical studies, *N nucifera* has been demonstrated to exert antiobesity effects by inhibiting carbohydrate and lipid absorption, stimulating lipolysis via β-adrenergic activation, increasing thermogenesis, and downregulating lipogenic genes.^[12,13,15–17]^ We reported that *P persica* reduces adiposity and hyperglycemia in obese mice and is more effective when combined with *N nucifera*.^[14,18]^ HT077, the combination of these 2 herbs, exerted antiobesity effects and decreased elevated triglycerides and glucose levels in mice fed a high-fat diet.^[18]^

Although traditional use and preclinical data support the clinical application of HT048 and HT077, a prospective randomized trial has yet to be performed to investigate the efficacy and safety of HT048 and HT077.

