### Objectives

1.1

This study primarily aims to examine whether HT048 and HT077 are superior to the placebo in reducing body fat mass and percent body fat in overweight subjects. The secondary objectives are to assess the effects of HT048 and HT077 on abdominal fat, body weight, BMI, waist and hip circumference, and serum lipids and adipocytokines concentrations, and to investigate the safety of HT048 and HT077.

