The primary efficacy endpoint is the change in body fat mass and percent body fat measured by DXA at week 12 from the baseline. The secondary efficacy endpoints are as follows:(1)the change in body fat mass and percent body fat measured by BIA at weeks 4, 8, and 12 from the baseline;(2)the change in visceral fat area, subcutaneous fat area, total abdominal fat area, and visceral fat/subcutaneous fat area ratio measured by abdominal CT at week 12 from the baseline;(3)the change in body weight at weeks 4, 8, and 12 from the baseline;(4)the change in BMI at weeks 4, 8, and 12 from the baseline;(5)the change in waist circumference, hip circumference, and waist circumference/hip circumference ratio at weeks 4, 8, and 12 from the baseline;(6)the change in blood lipids (total cholesterol, triglyceride, high density lipoprotein cholesterol, and low-density lipoprotein cholesterol) concentrations at week 12 from the baseline;(7)the change in serum leptin and adiponectin concentrations at week 12 from the baseline;(8)the change in body weight at week 16 from week 12; and(9)the change in BMI at week 16 from week 12.

Safety will be assessed on the basis of adverse events reported by participants or the principal investigator, abnormal laboratory results (hematology, biochemistry, and urinalysis), vital signs, and physical examination findings. Laboratory tests will be performed at screening, baseline, and week 12. Measurements of vital signs and physical examination will be performed at every visit.

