### Statistical analysis

2.8

The efficacy outcome data will be analyzed by using both intention-to-treat and per-protocol population. The intention-to-treat population will comprise all randomized participants and the per-protocol population will be composed of participants whose primary efficacy assessments were performed according to the protocol without major protocol violations, such as unmet inclusion/exclusion criteria or the use of prohibited medication. Participants whose compliance to treatment is less than 80% will be excluded from the per-protocol population. The safety outcome data will be analyzed by using a safety population, which will include participants who receive treatment at least once and have at least 1 safety assessment after treatment. Missing data will be replaced using the last observation carried forward method.

Continuous variables will be described as mean, median, standard deviation, and range (minimum and maximum), and categorical variables will be described as frequency and percentage. Analysis of covariance with the baseline measurements as a covariate will be performed to examine inter-group differences in the primary and secondary endpoints. Continuous variables will be compared by using an independent *t* test or Wilcoxon rank-sum test between the treatment and placebo groups, depending on normality of the distribution. In addition, differences within groups before and after the intervention will be compared by using a paired *t* test or Wilcoxon signed-rank test. Categorical variables will be presented as the frequency and percentage and compared by using either the Chi-square or Fisher exact test. Adverse events will be classified by the Common Terminology Criteria for Adverse Events from the National Cancer Institute (ver. 4.0). Probability values of <.05 with 2-tailed tests will be considered significant. The statistical analysis will be performed with SPSS Statistics software version 25 (IBM, Chicago, IL). No interim analyses will be performed.

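### Continuous safety measures are, on the natural reading of section 2.8, compared without baseline adjustment although their baselines are collected; this is valid but less precise than the ANCOVA used for efficacy

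*Protocol article*

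**What the plan says.** Section 2.8 (Statistical analysis) states: "Analysis of covariance with the baseline measurements as a covariate will be performed to examine inter-group differences in the primary and secondary endpoints". Section 2.6 sets out what those endpoints are. The primary endpoint is DXA body fat. The secondary list opens with "The secondary efficacy endpoints are as follows" and has nine items, none of them a vital sign or a safety laboratory value. Safety follows in its own paragraph.

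The next sentence of section 2.8 reads: "Continuous variables will be compared by using an independent *t* test or Wilcoxon rank-sum test between the treatment and placebo groups", with the choice depending on normality. It names no particular variables and does not say whether follow-up values or changes are compared. Within each arm, "differences within groups before and after the intervention will be compared by using a paired *t* test or Wilcoxon signed-rank test".

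The baseline values exist. Section 2.6 says "Measurements of vital signs and physical examination will be performed at every visit" and "Laboratory tests will be performed at screening, baseline, and week 12". Section 1.1 includes safety among the secondary objectives: "and to investigate the safety of HT048 and HT077".

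**The concern.** The plan collects the covariate for efficacy and safety alike but, as worded, uses it only for efficacy. Once the efficacy endpoints are taken out, the t test or rank-sum sentence is the only between-group method left for continuous data, and section 2.8 also defines a population for analysing safety outcomes. The within-arm paired tests do not fill the gap, because they give no comparison with placebo.

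What is at stake is how finely the trial can estimate a shift in blood pressure, pulse or a laboratory value. The article calls this a first-in-human trial, plans no data monitoring committee (section 2.9), and bases its sample size on percent body fat alone (section 2.7). No power is stated for any safety variable. With the numbers fixed, an efficient analysis is the cheapest way to narrow the safety confidence intervals.

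**Working it through.** **The plan's own figure.** Section 2.7 assumes changes of 2.2 and 0.5 (difference 1.7), SD 2.14, two-sided 5% and 80% power. The normal approximation gives n = 2 × (2.14 × (1.960 + 0.842) / 1.7)² = 24.9, so 25 per arm, as stated. Then 25 × 1.28 = 32, 32 / 0.8 = 40 and 3 × 40 = 120. All of this reproduces. It concerns percent body fat only and says nothing about safety variables.

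**Inputs for the safety comparison**
- From section 2.7: 40 per arm randomized, 32 per arm left after 20% drop-out. From section 2.8: two-sided 5%.
- Assumed, because the documents give neither: the correlation ρ between baseline and follow-up (0.3 to 0.8), and a true shift of 0.5 SD of the follow-up value. The SD is taken as equal at both times.

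**Formulas.** Variance of the between-arm difference, relative to a t test on raw follow-up values:
- raw follow-up value: 1
- change from baseline: 2(1 − ρ)
- ANCOVA: 1 − ρ²

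ANCOVA against change is therefore (1 − ρ²) / (2(1 − ρ)) = (1 + ρ)/2. Power comes from the noncentral t distribution with noncentrality 0.5 / √(v × 2/n), where v is the relative variance. Degrees of freedom are 2n − 2, or 2n − 3 for ANCOVA. For n = 32 and ρ = 0.5 the noncentrality is 0.5 / √(2/32) = 2.00 for raw values, the same for change (v = 1), and 2.00 / √0.75 = 2.31 for ANCOVA.

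| ρ | Variance, ANCOVA / raw | Variance, ANCOVA / change | Power at n = 32: raw, change, ANCOVA | Power at n = 40: raw, change, ANCOVA |
|---|---|---|---|---|
| 0.3 | 0.91 | 0.65 | 50%, 38%, 54% | 60%, 46%, 64% |
| 0.5 | 0.75 | 0.75 | 50%, 50%, 62% | 60%, 60%, 72% |
| 0.7 | 0.51 | 0.85 | 50%, 72%, 79% | 60%, 81%, 87% |
| 0.8 | 0.36 | 0.90 | 50%, 88%, 91% | 60%, 94%, 96% |

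The two comparisons move in opposite directions. Against raw values the gain grows with ρ; against changes it shrinks. ANCOVA is ahead of both at every ρ tried. The table is for the t test; the rank-sum test was not computed.

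**The case against.** The strongest reply is that the article never says safety variables will be tested unadjusted. The t test sentence could be meant for baseline characteristics, and the model for each vital sign or laboratory value is routine content for a full protocol or SAP, neither of which is shown. This stands in part: the reading is reached by elimination. But the article does name a method for continuous variables without limiting it, so a later document would have to narrow or depart from that wording. If the sentence does mean baseline characteristics only, saying so removes the ambiguity.

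A second reply is that a t test on changes already uses baseline. That is correct, and at ρ = 0.8 with 32 per arm ANCOVA then adds only 3 points of power (88% to 91%). At lower correlations the gain is larger.

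Third, safety is also judged on adverse events and abnormal results, which fall under the Chi-square or Fisher provision. That is so, and those comparisons are unaffected by this point.

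Finally, a blanket move to ANCOVA would discard the plan's provision for non-normal data. That is a fair warning, and the fix has to keep such a provision.

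A reader might go further and link the point to a cardiovascular effect of HT077, because the Introduction mentions "stimulating lipolysis via β-adrenergic activation, increasing thermogenesis". The documents do not support this. The statement concerns *N nucifera*, one of HT077's two components, in preclinical work on antiobesity effects. It is not made about HT077 itself, and no cardiovascular effect is stated. The point does not depend on it.

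**Conclusion.** The point holds as a minor matter of precision. On the natural reading, continuous safety measures get a valid but less efficient comparison than efficacy measures, with the baseline data already in hand. For ρ between 0.3 and 0.7, ANCOVA would save 9% to 51% of the variance against raw follow-up values, or 35% to 15% against changes. The power illustration (about 50% against 62%) rests on 32 per arm, a 0.5 SD shift and ρ = 0.5; the shift and the correlation are assumptions.

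Two stronger readings should be avoided. A reader might infer that the safety comparison is biased; it is not, because allocation is randomized. A reader might also infer that a non-significant safety result would be presented as absence of effect; the article states no such rule and no safety hypothesis.

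**What to change.** In section 2.8, say which variables the t test or rank-sum sentence covers, and extend the ANCOVA sentence to continuous safety measures:

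- Compare each product with placebo by ANCOVA with the baseline value as covariate, for vital signs at weeks 4, 8, 12 and 16 and laboratory values at week 12. Report the adjusted difference with its 95% confidence interval.
- For clearly non-normal variables, such as liver enzymes, use ANCOVA on the log scale or a rank-based ANCOVA.
- Keep the Chi-square or Fisher test for counts of abnormal results.

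The cost is a few sentences of wording, a few more model runs, and a transformation for skewed variables, whose results then need reporting on the transformed or ratio scale. No new data, visits or participants are needed.

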### Data management and monitoring

2.9

The participating site will be regularly monitored by well-trained clinical research associates from a contract research organization in compliance with standard operating procedures. Source data verification during on-site monitoring visits, double data entry, and validation (eg, range checks) will be performed to ensure the data quality. All documents and data collected from participants will be kept confidential in a separate and secure location and will not be provided to any other third party without permission of the principal investigator and sponsor. A data monitoring committee will not be needed because the intervention is low risk and there will be no interim analyses.

### Harms

2.10

All adverse events will be monitored and recorded, irrespective of causality. The principal investigator will evaluate the severity of symptoms and the causal relationship to the investigational product. If a serious adverse event occurs, it will be reported to the Institutional Review Board and sponsor within 24 hours, and the participation will be discontinued. Participants will be compensated for medical expenses related to injuries that are confirmed to be caused by the trial procedure or investigational products.

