### Interventions

2.4

The investigational product will be produced by COSMAX BIO Inc (Jecheon, Chungcheongbuk-do, Republic of Korea). The active product is a 500 mg tablet containing either 333.3 mg HT048 (125.8 mg of *C unshiu* extract and 207.5 mg of *C pinnatifida* extract) or 133.3 mg HT077 (57.3 mg of *N nucifera* extract and 76.0 mg of *P persica* extract). The active and placebo tablets are identical in shape, size, and color. Participants will be orally administered either 3 active or placebo tablets per dose, twice a day (morning and evening after meals) for 12 weeks. The daily doses are 2000 and 800 mg for HT048 and HT077, respectively. Participants will receive a 1-month supply of investigational product at baseline and weeks 4 and 8 and will be encouraged to continue to follow the prescribed dosage regimen. At weeks 4, 8, and 12, unused tablets will be returned and counted for the evaluation of participants’ compliance.

Participants will be advised to maintain their usual diet and exercise levels during the study. Participants will be prohibited to receive medicines and functional foods that can affect body weight and body fat during the study. Medicines, functional foods, exercise therapy, and diets that participants previously maintained before enrollment may be allowed if necessary at the investigator's discretion. Information regarding all concomitant medications, including the product or ingredient name, dosage, and duration, will be recorded at every visit.

Intervention will be discontinued under the following circumstances:(1)if a serious adverse event occurs;(2)if a participant has used a drug or physical procedure that could affect body weight and body fat;(3)if a participant wish to discontinue study participation;(4)if difficulties in assessments occur owing to administrative reasons, such as violations in dosage method or visit schedule; and(5)if difficulties in follow-up occur owing to a participant's personal reasons.

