### Outcome measures and endpoints

2.6

DXA will be used to assess body fat mass and percent body fat at baseline and week 12 as the primary outcome measure. In addition, body fat mass and percent body fat will be measured by BIA at baseline and weeks 4, 8, and 12. DXA and BIA are representative methods for assessing body composition, and the correlation between the 2 measurements for body fat mass and percent body fat are generally known to be good in both sexes.^[19,20]^ Abdominal CT will be used to measure visceral fat area, subcutaneous fat area, total abdominal fat area, and visceral fat/subcutaneous fat area ratio at baseline and week 12. CT scanning will be performed between the fourth and fifth lumbar vertebrae. With high accuracy, CT is considered as the reference method for measuring visceral and subcutaneous fat.^[21]^ Body weight and BMI will be measured at baseline and weeks 4, 8, 12, and 16. Waist circumference, hip circumference, and waist circumference/hip circumference ratio will be assessed at baseline and weeks 4, 8, and 12. According to the World Health Organization guidelines, waist circumference will be measured at the midpoint between the lower margin of the last palpable rib in the midaxillary line and the top of the iliac crest, and hip circumference will be measured at the largest circumference of the buttocks.^[22]^ Serum lipids (total cholesterol, triglyceride, high density lipoprotein cholesterol, and low-density lipoprotein cholesterol) and adipocytokines (leptin and adiponectin) concentrations will be assessed at baseline and week 12.

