### Withdrawal and dropout

2.11

Participants may withdraw at any time without penalty if they wish to discontinue their participation. The investigator may withdraw a participant if he/she considers it necessary for medical or administrative reasons (severe adverse events, significant protocol violations, etc). When a participant is withdrawn from the study, the date of withdrawal and the reason for withdrawal will be recorded.

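### A serious adverse event ends participation in section 2.10 but only the intervention in section 2.4; anyone removed before week 12 enters the ITT analysis with a change of zero

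*Protocol article*

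**What the plan says.** Three sections of the Protocol article cover early stopping.

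- **Section 2.10 (Harms)**, on a serious adverse event: "it will be reported to the Institutional Review Board and sponsor within 24 hours, and the participation will be discontinued". The rule is mandatory and concerns participation.
- **Section 2.4 (Interventions)** opens its list with "Intervention will be discontinued under the following circumstances". The list includes a serious adverse event, use of a drug or procedure that could affect weight or fat, and "if difficulties in assessments occur owing to administrative reasons, such as violations in dosage method or visit schedule". It concerns the product and does not mention follow-up.
- **Section 2.11 (Withdrawal and dropout)**: "The investigator may withdraw a participant if he/she considers it necessary for medical or administrative reasons", with severe adverse events and significant protocol violations as examples. This is discretionary and concerns the study. It adds: "When a participant is withdrawn from the study, the date of withdrawal and the reason for withdrawal will be recorded".

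Two further statements determine the consequence. Section 2.8: "The intention-to-treat population will comprise all randomized participants", with last observation carried forward (LOCF) for missing data. Section 2.6: "DXA will be used to assess body fat mass and percent body fat at baseline and week 12 as the primary outcome measure".

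**The concern.** One trigger, a serious adverse event, has two stated consequences: the product stops (2.4), or participation ends (2.10). Section 2.11 adds a discretionary route with a different adjective, severe instead of serious. Sites could follow these sections in different ways.

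The difference matters for the primary analysis. An analysis of everyone randomised is meant to use the outcomes of people who stopped treatment. If the plan removes them before the only post-baseline DXA, it loses outcomes that could have been measured. The grounds for removal, such as adverse events or significant violations, may be related to outcome and to arm, so the loss need not be neutral.

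Safety data are also at stake. The trial describes itself as first-in-human, has no data monitoring committee (section 2.9), and presents its 4-week post-treatment follow-up as a strength (Discussion). As section 2.10 is worded, participants with serious events would leave that follow-up.

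**Working it through.** **1. The provisions side by side**

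| Section | Trigger | What ends | Force |
|---|---|---|---|
| 2.4 | Serious adverse event; weight-affecting drug or procedure; dosing or visit violations; others | Intervention | Will |
| 2.10 | Serious adverse event | Participation | Will |
| 2.11 | Medical or administrative reasons, e.g. severe adverse events, significant violations | Study participation | May |

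Ending participation implies stopping the product, so 2.4 and 2.10 can both be obeyed. They still give different answers on whether assessments continue.

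**2. What happens to someone removed before week 12**

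- DXA has one post-baseline time point (2.6). The last observation available is baseline, so LOCF gives a change of exactly 0. The same holds for CT, lipids and adipocytokines. Weight, BMI, BIA and waist or hip measures may have a week-4 or week-8 value to carry.
- Safety laboratory tests are scheduled at screening, baseline and week 12 (2.6). Removal before week 12 loses the only post-baseline set, and the week-16 visit.
- This follows for removal under 2.10 or 2.11. For those who only stop the product under 2.4, the text does not say whether follow-up continues.

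**3. The plan's own sample size (section 2.7)**

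Inputs: difference 2.2 − 0.5 = 1.7 points, SD 2.14, two-sided 5%, power 80%.

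n = 2 × (1.960 + 0.842)² × 2.14² / 1.7² = 24.9, i.e. 25 per group. Then 25 × 1.28 = 32; 32 / 0.8 = 40; 3 × 40 = 120. The plan's figures reproduce and are not disputed.

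**4. Effect of the zero fill**

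Assumption: a share p of each arm has no week-12 DXA, for any reason, and is set to 0. The expected difference is 1.7 × (1 − p).

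- p = 5%: 1.7 × 0.95 = 1.62
- p = 20% (planned dropout, 8 per arm, 24 of 120): 1.7 × 0.80 = 1.36

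With 40 per arm analysed and per-arm variance (1 − p) × 2.14² + p(1 − p) × mean², the SD at p = 20% is 2.02. Two-sample t-test power is then about 85%, against 94% if all 40 were observed.

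Unequal shares (illustrative; the documents give none):

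- 30% active, 10% placebo: 2.2 × 0.7 − 0.5 × 0.9 = 1.09, power about 65%
- 10% active, 30% placebo: 2.2 × 0.9 − 0.5 × 0.7 = 1.63, power about 95%

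The estimate thus depends on how removal splits between arms.

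**5. What bringing people back would change**

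Assume equal 20% loss, half of whom return (10% of each arm), and let r be the fraction of the 1.7-point effect present in returners who are off product. The expected difference is 0.8 × 1.7 + 0.1 × 1.7 × r = 1.36 + 0.17r. The gain is 0 at r = 0 and 0.17 at r = 1.

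**The case against.** The strongest objection is that much of this rests on silence in a condensed article. Section 2.12 refers to a full protocol (version 3.1) that is not public, and Table 1 is not shown, so an early-termination assessment cannot be excluded. Section 2.11 says that date and reason are recorded; it does not say that nothing else is. These points stand, and they limit the claim about people who merely stop the product. They do not remove the explicit end of participation in section 2.10 or its mismatch with section 2.4.

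Serious events may also be few, since section 2.9 calls the intervention low risk. All adverse events are to be monitored and recorded regardless of cause, and treated participants with a post-treatment safety assessment stay in the safety population. The safety loss is therefore confined to scheduled assessments after removal.

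A reader might infer three stronger things that the documents do not support:

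- **That these rules cause the 20% loss.** The 20% covers every cause, including voluntary withdrawal and loss to follow-up. No rate of serious adverse events or violations is given. Moreover, the fall from 1.70 to 1.36 comes from the zero fill, and at equal 20% loss power still exceeds 80%.
- **That bringing half of them back would restore the difference to 1.53.** That is only the upper end, 1.36 + 0.17, and requires people off product to show the full effect. With no retained effect it stays at 1.36.
- **That ITT becomes almost a per-protocol analysis.** It does not. Early leavers remain in ITT at zero change but are absent from per-protocol, while poorly compliant completers keep their observed DXA in ITT and are excluded from per-protocol.

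**Conclusion.** The point holds in a limited form. Sections 2.4, 2.10 and 2.11 must be reconciled on what ends after a serious adverse event or a significant violation: the product, the assessments, or both. As written, a serious adverse event before week 12 ends participation, and discretionary withdrawal can do the same. Those people are then analysed at zero change on the primary endpoint and miss the week-12 laboratory tests and the week-16 visit.

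The number affected cannot be derived from the documents. If half of an equal 20% loss returned, the expected difference would change by 0 to 0.17 points, assuming that between none and all of the effect remains off product. The case for change therefore rests on observed outcomes in the all-randomised analysis and more complete safety data, not on a larger estimated effect. No view is taken on when treatment should stop. The sponsor should make the change, but the documents do not show that the trial's conclusion depends on it.

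**What to change.** Leave the rules for stopping the product and the investigator's medical discretion as they are. Reconcile sections 2.4, 2.10 and 2.11, and add three statements:

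1. Stopping the investigational product does not by itself end data collection.
2. Participants who stop are invited to the already scheduled week-12 DXA, weight and laboratory assessments and to the week-16 visit, unless they withdraw consent to data collection or the investigator judges an assessment medically inappropriate.
3. Treatment status (on or off product) is recorded at each visit.

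The cost is a short protocol amendment and a modest effort to bring stopped participants back. The scans and visits are already planned for all 120. If the full protocol or Table 1 already provides for this, aligning the wording of section 2.10 is enough.
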